**Fig. 1 Fig1:**
[figure not shown]
General population study flow. BHI, Bladder Health Instrument; CASI, Computer Assisted Self Interview; PAPI, Paper and Pencil self-Interview; RA, Random Assignment

Respondents, regardless of initial mode assignment, who fully complete the validation survey packet are subsequently re-contacted within 2–4 weeks and randomized 2:1 to complete either (a) a retest of the PLUS-BHI in the same mode (PAPI or CASI) followed by a 2-day bladder symptom diary (Additional file 1) or (b) to only complete a 2-day bladder symptom diary. The retest version of the PLUS-BHI includes 2 Guyatt transition rating items [26] to identify changes to a person’s health, which serve as an anchor for stability in the retest reliability analysis, as well as the PLUS-BHI items. The 2-day bladder symptom diary is mailed to the respondent independent of mode of PLUS-BHI completion. Up to 4 contact attempts are made for completion of the retest version of the PLUS-BHI and up to 3 contact attempts for completion of the 2-day bladder symptom diary. Respondents receive $10 compensation for completing each of the re-test and/or 2-day bladder symptom diary.

The NIDDK has an expectation of grant award recipients to support data sharing, facilitated by their data repository. To assess the impact of language related to data sharing in the consent process, each address is randomly assigned (1:1) to have the request for permission to share anonymized data with the NIDDK repository either at the end of the PLUS-BHI validation packet or to receive the request separately (e-mail for CASI, separate letter for PAPI). This allows for evaluation of potential threat bias influence on completion of the survey altogether and also the degree of endorsement separate from completion of the survey [23].

#### Clinical center populations

The study flow for the general population cohort is outlined in Fig. 2. Once eligibility criteria are established (Table 1), verbal consent is obtained; and participants are enrolled and randomized to PAPI vs. CASI mode 1:2 in blocks of 3, stratified by center. Those who do not have email capability are offered participation in the PAPI arm. Those assigned to PAPI mode are mailed the same survey packet described for the general population. Those participants assigned to the CASI version are emailed a unique link to complete the surveys and PLUS-BHI validation material online, which are captured directly via REDCap [27]. Non-respondents are mailed or emailed replacement packets up to three times every 15 days.

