**Methods:**

Three samples of women are being recruited: a sample from a nationally representative general population and two locally recruited clinical center samples—women with a targeted range of symptom severity and type, and a postpartum group. The general population sample includes 694 women, 18 years or older, randomly selected from a US Postal delivery sequence file. Participants are randomly assigned to electronic or paper versions of the bladder health instrument along with a battery of criterion questionnaires and a demographic survey; followed by a retest or a two-day voiding symptom diary. A total of 354 women around 7 clinical centers are being recruited across a spectrum of self-reported symptoms and randomized to mode of completion. They complete the two-day voiding symptom diary as well as a one-day frequency volume diary prior to an in-person evaluation with a standardized cough stress test, non-invasive urine flowmetry, chemical urine analysis and post void residual measurement. Independent judge ratings of bladder health are obtained by interview with a qualified health care provider. A total of 154 postpartum women recruited around 6 of the centers are completing similar assessments within 6–12 weeks postpartum. Dimensional validity will be evaluated using factor analysis and principal components analysis with varimax rotation, and internal consistency with Cronbach’s alpha. Criterion validity will be assessed using multitrait-multimethod matrix including correlations across multiple data sources and multiple types of measures.

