#### Clinical center populations

The general clinical center population of women are being recruited from the community and medical practices surrounding the PLUS clinical research centers: Loyola University Chicago, University of Alabama at Birmingham, University of California San Diego, University of Michigan, University of Pennsylvania, Washington University in St Louis, and Yale University. Potential participants are screened on inclusion/exclusion criteria (Table 1) and purposive sampling conducted with the intention of representing the spectrum of bladder health and LUTS. To accomplish this, a modified version of the Patient Perception of Bladder Condition (PPBC) questionnaire is used to categorize participants into one of four equal size groupings [25]. Using the question “Which of the following statements best describes any problems you may have with peeing or your bladder?”: women are screened into healthy with no reported problems (PPBC response = 1), mild bladder problems (PPBC response = 2 or 3), moderate bladder problems (PPBC response = 4), or severe bladder problems (PPBC response = 5 or 6). When a quota is full (i.e., severe), individuals are screened out (Table 3).

**Table 3 Tab3:** VIEW target enrollment of clinical center population bladder symptom strata

Symptom strata	Self-report of LUTS-PPBC				
	Healthy	Mild	Moderate	Severe	Total
Frequency	90	15	15	15	45+
Incontinence		15	15	15	45+
Urgency		15	15	15	45+
Pain/discomfort		15	15	15	45+
Peeing/flow		15	15	15	45+
Urinary tract infection		15	15	15	45+
Total	90	88	88	88	354

LUTS, Lower urinary tract symptoms; PPBC, Patient perception of bladder condition: The four categories of Healthy to Severe map to PPBC responses to the question “Which of the following statements best describes any problems you may have with peeing or your bladder?”: healthy with no reported problems (PPBC response = 1), mild bladder problems (PPBC response = 2 or 3), moderate bladder problems (PPBC response = 4), or severe bladder problems (PPBC response = 5 or 6)

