### Study administration

#### General population

The study flow for the general population cohort is outlined in Fig. 1. All households in the DSF sample frame are mailed a pre-notification letter including a $2.00 bill and a tri-fold color brochure describing the study, with a request for participation by the female in the household, age 18 or over with the most recent birthday. Households are randomized 1:2 to PAPI or CASI. The imbalanced randomization reflects an expected lower response rate from CASI [23]. For those randomized to PAPI, the first PLUS-BHI packet mailing includes $10 as incentive and a stamped envelope addressed to the Scientific and Data Coordinating Center (SDCC). Non-respondents are sent replacement packets up to 4 times. Those randomized to CASI are asked to provide a valid email address using the provided postage paid return envelope. Respondents who do not provide an email are necessarily assigned to the push-to-web group, wherein future paper mailings include an electronic link for online survey completion. Households who do provide an email address are randomized to either the push-to-web group or to receive an email with a link to the survey (referred to as the web primary group). This second randomization allows a full comparison of respondents who fully elect to respond via electronic mode to those who do not. Those in the web primary group are additionally randomized 1:1 to receive $5 thank you for providing an e-mail address. A total of four follow-up packets are mailed to non-respondent households wherein the final contact includes a paper version of the survey.

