### Strengths and limitations

One of the primary intended uses of the validated PLUS-BHS is to establish a U.S. general population estimate of women’s bladder health, across the life course. To ensure the PLUS-BHS is valid for this inference it is essential to validate using a national general population sample of women. Some of the challenges in conducting national population research is the identification of a representative sample frame, minimizing the well-known problem of coverage error. With survey methods sampling, the DSF with household level enumeration of every known mailing address within the U.S. is the address base sampling frame with the lowest coverage error that exists. The use of random assignment of both general population participants as well as, general clinical participants to the multiple modes (PAPI, CASI and within CASI Web primary as well as push to web) allows a valid and unconfounded comparison of differences in both response rate, item-response as well as distributional differences across mode. The inclusion of clinical samples using community based recruitment allows a clinical evaluation of women across the spectrum of potential bladder health. The inclusion of objective clinical test data provides the “hard ratings” required as a standard of evidence for valid inference with the intended use of the PLUS-BHS. A major strength of our validation work is the inclusion and evaluation of women during the postpartum period. While we would not expect women’s bladder health to be considered stable during pregnancy, we expect the postpartum period to be a factor in women’s bladder health over their lifetime.

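### Fixed blocks of 3 at 1:2 within centre make up to 44% of clinical-centre mode assignments predictable, so calling that comparison unconfounded is too strong

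*Protocol article*

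**What the plan says.** The section on study administration for the clinical center populations gives the order of steps: "Once eligibility criteria are established (Table 1), verbal consent is obtained; and participants are enrolled and randomized". It then fixes the scheme: "participants are enrolled and randomized to PAPI vs. CASI mode 1:2 in blocks of 3, stratified by center". The assignment cannot be hidden afterwards. Women in the PAPI arm are mailed a packet, and "Those participants assigned to the CASI version are emailed a unique link to complete the surveys and PLUS-BHI validation material online". There is also a route into paper outside the random assignment: "Those who do not have email capability are offered participation in the PAPI arm".

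The abstract gives the size of this sample: "A total of 354 women around 7 clinical centers are being recruited across a spectrum of self-reported symptoms and randomized to mode of completion". The section on study populations describes recruitment as "purposive sampling conducted with the intention of representing the spectrum of bladder health and LUTS". It sets PPBC groups that close when full, a second screen by symptom type, and a minimum number per age stratum at each centre.

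The general population sample is handled differently: "Households are randomized 1:2 to PAPI or CASI", drawn from a postal address frame, with no block size stated. Postpartum women choose their mode and are not part of any randomised mode comparison.

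The strengths and limitations section says that random assignment, in both the general population and the general clinical participants, "allows a valid and unconfounded comparison of differences in both response rate, item-response as well as distributional differences across mode".

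**The concern.** Three is the smallest block that can deliver a 1:2 ratio, so this is the most predictable permuted-block scheme available. Once the PAPI place in a block is used, the rest of that block is CASI. If the first two places are CASI, the third is PAPI. Blocks run within a centre, so the last one or two assignments at that site are enough to work this out. Holding the list centrally does not prevent that.

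Prediction matters only where someone can act on it. Purposive sampling to quotas gives legitimate reasons to choose whom to approach and when. If the expected mode influenced those choices, the PAPI and CASI groups could differ in age or symptoms before anyone answered a question.

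Evaluating mode effects is the second of the article's two stated objectives. Under the analysis plan, items that differ significantly by mode are considered for removal, and mode is compared separately in the general population and clinical samples. A difference created by who was enrolled could then be read as a mode effect.

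**Working it through.** The documents give no figure for predictability, so there is none to reproduce. The inputs are the 1:2 ratio and block size of 3 within centre (study administration, clinical center populations), and 354 women at 7 centres (abstract).

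**Certain assignments.** Write P for PAPI and C for CASI. A block has three equally likely orders. An assignment is certain when all the places left in the block are the same mode.

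- PCC: places 2 and 3 are certain, both C. Count 2.
- CPC: place 3 is certain, C. Count 1.
- CCP: place 3 is certain, P. Count 1.

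The total is 4 certain of 9 places, or 44.4%. Of these, 3/9 are CASI and 1/9 is PAPI. In women:

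- all: 354 × 4/9 = 157.3
- CASI: 354 × 3/9 = 118
- PAPI: 354 × 1/9 = 39.3

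This is half of the CASI assignments (118 of 236) and one third of the PAPI assignments (39.3 of 118).

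**Per centre.** 354/7 = 50.6 women, of whom 50.6 × 4/9 ≈ 22 are predictable. The documents do not say how many centres, if any, could track assignments. The range is therefore from 0 (no centre) to about 157 women (all seven), at about 22 per centre.

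**Best-guess accuracy.**

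- Place 1: 2/3.
- Place 2: 1/3 × 1 + 2/3 × 1/2 = 2/3.
- Place 3: 1.
- Mean: (2/3 + 2/3 + 1)/3 = 7/9 = 77.8%.

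Always guessing CASI gives 66.7%, so tracking adds 11.1 percentage points.

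**Alternatives.** Fixed blocks were enumerated exactly. Mixed blocks were simulated with 51 women per centre, 3,000 replicates and equally likely sizes; the guesser knows the set of possible sizes but not the size of any given block.

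| Scheme | Certain | Best guess |
|---|---|---|
| Fixed 3 (as planned) | 44.4% | 77.8% |
| Fixed 6 | 28.9% | 74.4% |
| Fixed 9 | 21.4% | 72.8% |
| Mixed 3 and 6 | about 10% | about 75.5% |
| Mixed 3, 6 and 9 | about 4% | about 73.6% |

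**The case against.** A reader might infer that recruiting staff do know 44% of assignments in advance. The documents do not say so. The article does not state who holds the list, who sends packets and links, whether recruiters see earlier assignments, or whether they were told the block size. A condensed article may leave all of that to the full protocol. Women without email who enter the PAPI arm could also blur the tracking, since the text does not say whether they use a place in a block. So 44% is a ceiling. It is not an empty one: the article prints the block size while describing recruitment as ongoing.

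A reader might also infer that the randomised mode comparison as a whole is undermined. That goes too far, for four reasons.

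- Predictability causes bias only if someone changes whom or when they enrol. The arms are two versions of one questionnaire, and the documents show neither a motive nor any steering.
- Assignment already follows eligibility and verbal consent. This limits, but does not remove, the scope for steering, because the choice of whom to approach comes earlier.
- Only 1 in 9 assignments is a certain PAPI place. The other predictable places are CASI, where steering would mean delaying or withholding enrolment.
- The general population comparison has no recruiter choosing participants and is analysed separately, so it offers a check. Flagged items are considered for removal, not removed automatically.

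Finally, varied blocks help less with guessing than with certainty: best-guess accuracy falls only from 77.8% to about 73.6%. That stands, but the places known for certain are the ones most open to deliberate steering, and these fall from 44% to about 4%.

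**Conclusion.** The point holds as an avoidable weakness in one of the two randomised mode comparisons. In the clinical-centre sample, up to 44% of assignments (about 157 of 354: about 39 PAPI and 118 CASI) are determined by earlier ones. Reaching that ceiling assumes that staff know the block size, know where blocks start and see each earlier assignment at their centre. Bias assumes further that they act on it, which nothing in the documents shows.

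The size of any resulting bias cannot be computed from the documents. They do support a narrower conclusion: this scheme leaves the clinical-centre comparison open to selection bias, so describing it as unconfounded is too strong for that sample. The general population comparison is not affected by this point. Severity is minor.

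**What to change.** 1. For remaining clinical-centre enrolment, replace the fixed block of 3 with randomly varied sizes, for example 3, 6 and 9. Do not disclose the sizes to centres, and release each mode centrally, keeping the present order of eligibility, verbal consent and then assignment.
2. For all randomised clinical-centre women, compare age, PPBC stratum and symptom type by assigned mode, and adjust the clinical-centre mode comparison for them. The study already screens on these variables, so no new data are needed.
3. In the strengths and limitations section, qualify the claim of an unconfounded comparison for the clinical-centre sample.

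The cost is a new randomisation list, a few extra analyses and slightly looser 1:2 balance within a centre. Blocks already completed cannot be repaired. For those women only the comparison and adjustment in step 2 are available, and these cover measured characteristics only.

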**Fig. 2 Fig2:**
[figure not shown]
Clinical center sample study flow. BH, Bladder Health; BHI, Bladder Health Instrument; CASI, Computer Assisted Self Interview; PAPI, Paper and Pencil self-Interview; RA, Random Assignment. *Note*: Postpartum sample N = 154 and are not randomized to BHI mode of administration

Participants who complete the initial materials are contacted and scheduled for an in-person clinical evaluation. Upon scheduling they are mailed a decorative box containing a copy of the written consent form, the 2-day bladder symptom diary (Additional file 1), a 1-day frequency-volume bladder dairy (Additional file 2), a voiding hat to measure urine volumes, and detailed instructions for completion of all material. Participants are contacted at least 4 days prior to the clinical evaluation to ensure completion of diaries prior to the visit.

On the day of the in-person evaluation, participants proceed with written informed consent, and bladder diaries are reviewed to confirm completion. Participants undergo an interview with a bladder health judge followed by clinical testing procedures to obtain the objective measures of bladder function outlined below. Participants receive prorated compensation up to $100 for completion of the study.

Women recruited for the postpartum population are allowed to select their preferred mode of administration rather than be randomized given the additional demands of completing study procedures for new mothers. The survey packet is sent to be completed within the 6–12 weeks postpartum window. Otherwise the steps are identical to the general clinical center population with respect to the judge assessments and in-person clinical evaluation conducted.

### Measures

Demographics items include both standard demographics as well as items to assess gender identification and sexual orientation. Items to assess general medical history and history of pelvic floor disorders are included. The survey packet also includes items to assess current LUTS and validated measures that serve as external criterion in establishing external validity. Details of the criterion instruments are further described below (Table 4). Dependent on branching, the number of items a respondent is presented ranges from 63 to 90 items. The total PAPI survey length, inclusive of all self-report measures, is 49 pages.

**Table 4 Tab4:** External criterion measures for validation assessment

Measure	Data source	Data method	Validation type
*Same source, same method (self-reported measures)*			
PLUS-BHI	Self	Survey	–
MOS-SF 36*	Self	Survey	Convergent
KHQ	Self	Survey	Convergent
UDI-6	Self	Survey	Convergent
POPDI	Self	Survey	Divergent
CRADI	Self	Survey	Divergent
BFLUTS	Self	Survey	Convergent
*Same source, different method*			
Bladder diaries: 1-day 2-day	Self	Activity log	Convergent
*Different source, different method*			
Judge BH rating: Aided Unaided	Other/expert	Qualitative	Convergent Divergent
*Different independent source, different method (objective measures)*			
PTT	Other/technical	Volume calculation	Convergent Divergent
Uroflowmetry	Voiding dynamics	Rate calculation	Convergent Divergent
PVR volume	Imaging	Volume calculation	Convergent Divergent
Urinalysis	Dipstick/biologic	Standardized lab Analysis	Convergent Divergent

^*****^Ten selected items from the Medical Outcome Study Short Form Health Survey (MOS SF-36)

KHQ, King’s Health Questionnaire; UDI, Urogenital Distress Inventory; BFLUTS, Bristol Female Lower Urinary Tract; PFDI-20, Pelvic Floor Distress Inventory; CRADI, colorectal and anal distress inventory; POPDI, pelvic organ prolapse distress inventory; PPT, Paper Towel Test for stress incontinence; PVR, post-void residual volume measurement by bladder scan

The intended use of a measure dictates the level of evidence required for inferential validity of a measure [28–30]. For this work, we are employing Campbell and Fiske’s multitrait-multimethod (MTMM) matrix to evaluate hierarchical and cumulative levels of evidence for convergent and discriminant validation of PLUS-BHS score [31]. External variables that rely on multiple and independent sources and methods of data collection in comparison to dimensions of the emergent PLUS-BHS will provide a high level of evidence to support inference of PLUS-BHS score as valid for research in the general population as well as clinical research. The external measures employed by this study were identified to satisfy the requirements of multiple sources and multiple methods: the referent method is self-report survey and the referent source is study participant.

#### Same source/same method measures

The PLUS consortium reviewed the quality and strength of evidence of available validated instruments that will provide measures of LUTS to serve as same source same method external criteria. Multiple instruments were assessed based on their potential ability to serve as a comparator to the bladder dimensions and domains of the bladder health model defined by the PLUS consortium [10]. Table 4 describes the instruments selected for use as criterion measures in the VIEW study. These include ten general health items selected from the Medical Outcome Study (MOS) Short Form-36 to evaluate association with the general bladder related health dimension of bladder health [32]. The King’s Health Questionnaire (KHQ) [33] and Urogenital Distress Inventory (UDI) short form [34] recommended as Grade A instruments for use in LUTS research were included [35]. However, the consortium determined that the KHQ and UDI may have insufficient items for evaluation of emptying function, thus the Bristol Female Lower Urinary Tract Symptoms (BFLUTS 3 voiding items (V1–V3)) [36] were included. Finally, the Pelvic Floor Distress Inventory (PFDI-20) [37], which includes the colorectal (CRADI) and prolapse (POPDI) subscales along with the UDI, were included with the expectation they will serve to evaluate divergence [37]. These items were administered to all three cohorts (general population, general clinical and postpartum clinical center cohorts) in the same mode as assigned for the PLUS-BHI completion.

